### 2.3. Prospective Study

#### 2.3.1. Participants

Forty patients (*n* = 20 hypertensives and *n* = 20 type II diabetics) will be recruited from the outpatient clinic at Alexandra Hospital, Singapore, during their routine clinic visits. The primary physician will identify potentially eligible participants and notify the research team. A research team member will discuss the project with the participant, screen for eligibility, and take consent. If a patient has both type II diabetes and hypertension, the treating physician will decide which study arm the patient should enrol on. Patients may be newly diagnosed or be those with established but poorly controlled disease. The presence of comorbidities and all prescribed medications will be tracked. The eligibility criteria are as follows: 

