##### Exclusion Criteria

Patients with cognitive impairment.

Patients with active cancer undergoing chemotherapy.

Patients on haemodialysis or peritoneal dialysis (which can cause rapid fluctuation of BP and blood sugar, respectively).

Pregnant patients.

Patients with type II diabetes and hypertension whose medications are changed simultaneously during their first clinic visit.

Patients with controlled HbA1c or blood pressure at baseline.

Serious concomitant disorders that would compromise the safety of the patient or their ability to complete the study. This may include a recent occurrence of stroke or sub-arachnoid haemorrhage in hypertensive patients, which necessitates tighter control, and occurrence of renal failure or lactic acidosis in patients with type II diabetes, which may warrant avoidance or reduction in metformin dose.

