#### 2.3.2. Outcome Measures

We will report on clinical and qualitative outcomes relating to CURATE.AI’s effect, implementation, and acceptability. The following clinical outcomes will be reported:Proportion achieving blood pressure and glycaemic control at four months.Average number of days until blood pressure or glycaemic control is first achieved.Proportion relapsing after disease control is achieved (i.e., high blood pressure).Proportion compliant with clinic follow-up.Proportion compliant with home monitoring of blood pressure or glucose.Number of dropouts.Proportion of dosing decisions recommended by CURATE.AI but not implemented at the physician’s discretion and the magnitude of difference.

The study’s main purpose is to explore the feasibility of the CURATE.AI system in clinical practice and not to establish efficacy or effectiveness. The clinical outcomes are included to show the preliminary effects of the intervention. Qualitative work will seek to understand the practicalities of using the system in clinical practice, identify implementation barriers and enablers that can inform future development of the system, and to advance the processes associated with using CURATE.AI.

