Participants will be followed up monthly for four months. Clinically, blood pressure may be controlled with medication within four to six weeks [33]. For type II diabetes, although traditionally changes in HbA1c are assessed every three months, emergent evidence suggests clinically relevant changes may occur as early as one month [34]. Based on these data, four months was deemed appropriate to observe clinical improvements as well as being a sufficient period to test the system. Clinic visits may be face-to-face or virtual as appropriate. If a dosage change is required at a clinic visit, hypertensive participants will be asked to monitor their ambulatory blood pressure for a single six-hour period at home (once hourly). A six-hour ambulatory blood pressure recording is equivalent to a twenty-four-hour reading [35]. Patients will then continue to monitor blood pressure twice daily, morning and evening, for up to seven days. Following any change of type II diabetic medications, patients will be asked to wear a continuous glucose monitoring device for a minimum of seven days at home (the maximum wear time is fourteen days). Monitoring will commence fifteen days after the dose change is initiated (for either hypertensives or type II diabetics), so a steady state can be reached before assessment. These data will feed back into the CURATE.AI system, and further recommendations on dose adjustment will be generated if required. The treating physician will regularly review remote monitoring data for safety. If the patient’s medication is changed entirely, recalibration with CURATE.AI is required. At the last clinic visit, patients will be interviewed using a semi-structured survey on their experiences with the CURATE.AI system. 

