#### 2.3.5. Data Analysis

All analyses will be conducted using STATA version 15.0 (STATA Corp, College Station, TX, USA). As appropriate, summary statistics will be presented as means with standard deviation, medians with interquartile ranges, and percentages. Clinical outcomes will be analysed separately for the hypertensive and type II diabetic groups. Blood pressure control is defined as a home or ambulatory blood pressure of less than 135/85 mmHg or office readings below 140/90 mmHg, unless otherwise defined by the treating physician [39]. Glycaemic control is defined as HbA1c < 7% [40] or glycaemic variability ≤ 36% or time in normal range (4.0 to 10.0 mmol/L) > 70% [41]. The proportion of patients achieving blood pressure control and glycemic control will be calculated by comparing the baseline reading to the four-month follow-up. A within-subject analysis of hypertensive and glycemic control will be conducted using the Chi^2^ or McNemar’s test, if cell counts are small (<5). The proportion achieving clinically relevant reductions in systolic and diastolic blood pressures by the four-month follow-up will be determined. The number of days until blood pressure or glycaemic control is first achieved will be calculated. The occurrence of relapse after control has been achieved (i.e., high blood pressure) will also be determined. 

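### Glycaemic variability ≤ 36% counts as glycaemic control on its own, so a patient with a sensor recording and steadily high glucose can be scored as controlled, mainly at follow-up

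*Protocol article*

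**What the plan says.** Section 2.3.5 (Data Analysis) of the protocol article defines glycaemic control as "HbA1c < 7% [40] or glycaemic variability ≤ 36% or time in normal range (4.0 to 10.0 mmol/L) > 70"%. Nothing there or elsewhere requires the variability criterion to be met together with one of the other two. The allowance for the treating physician to set a different target belongs to the blood pressure sentence, not the glycaemic one.

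The definition feeds two outcomes in section 2.3.2: "Proportion achieving blood pressure and glycaemic control at four months" and "Average number of days until blood pressure or glycaemic control is first achieved". A third is worded "Proportion relapsing after disease control is achieved (i.e., high blood pressure"), which names only blood pressure. For the before/after analysis, section 2.3.5 says the proportion controlled "will be calculated by comparing the baseline reading to the four-month follow-up", with a within-subject test.

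Two other places decide when the variability criterion can apply:

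- Section 2.3.3: after a change of diabetic medication, "patients will be asked to wear a continuous glucose monitoring device for a minimum of seven days at home", starting fifteen days after the change.
- Exclusion criteria: "Patients with controlled HbA1c or blood pressure at baseline" are not enrolled. Variability and time in range are not mentioned.

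On size, section 2.3.1 states: "Forty patients (*n* = 20 hypertensives and *n* = 20 type II diabetics) will be recruited".

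**The concern.** Two of the three criteria say how high glucose is. The third says only how much it moves relative to its own mean. Joined by *or*, the third overrides the other two: a patient who fails both HbA1c and time in range is still scored as controlled if glucose is stable, however high it is.

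At stake is what the diabetic group's control proportion and days to first control mean. Section 2.3.2 includes the clinical outcomes to show preliminary effects, and the Discussion says the data will inform a later efficacy evaluation. A proportion that mixes stable with controlled glucose is a poor basis for planning that study. If the variability route is available after entry but not at entry, some of the apparent improvement comes from the measurement schedule.

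**Working it through.** The article gives no figure on this point to reproduce, so the check is of the rule itself.

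**Inputs.** From the article: limits of 36% and 70%, range 4.0 to 10.0 mmol/L, 20 diabetic patients, monitoring from day 15 after a dose change, sensor worn for 7 to 14 days, monthly visits. Assumed: variability in percent is CV = SD/mean, and glucose within a patient is roughly lognormal (normal as a check).

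**1. Does the variability criterion limit glucose level?** Time in range is F(10) − F(4). For the lognormal, s² = ln(1 + CV²) and μ = ln(mean) − s²/2. For mean 14 and CV 25%:

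- s² = ln(1.0625) = 0.0606, so s = 0.246; μ = 2.639 − 0.030 = 2.609.
- F(10) = Φ((2.303 − 2.609)/0.246) = Φ(−1.24) = 0.107; F(4) = Φ(−4.97) ≈ 0.
- Time in range ≈ 11%.

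| Mean (mmol/L) | CV | Time in range, lognormal | Normal | Time in range > 70%? | CV ≤ 36%? |
|---|---|---|---|---|---|
| 8 | 30% | 80% | 75% | yes | yes |
| 10 | 25% | 55% | 49% | no | yes |
| 12 | 30% | 32% | 28% | no | yes |
| 14 | 25% | 11% | 12% | no | yes |
| 16 | 20% | 1% | 3% | no | yes |

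At a mean of 8 the two criteria agree in this example. From a mean of 10 upwards, every CV tried from 15% to 36% fails time in range and passes variability.

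**2. Direction.** Hold SD at 4 mmol/L. Mean 10 gives 4/10 = 40%, not met; mean 12 gives 4/12 = 33%, met. With the spread unchanged, the higher glucose passes.

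**3. Who can be scored this way?** Only patients with a recording. A recording ends 15 + 7 = 22 to 15 + 14 = 29 days after a dose change.

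- *Days to first control:* a dose change at baseline can yield a variability result from about day 22, before the first monthly visit.
- *Control at four months:* Table 1 marks the Baseline and Visit 1 to 3 columns for possible home monitoring, but not Visit 4. A current recording at Visit 4 is therefore expected mainly in patients whose dose changed at Visit 3. The article does not say whether older recordings are carried forward.

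**4. Baseline against follow-up.** Take a patient with HbA1c ≥ 7%, time in range ≤ 70%, CV ≤ 36% and no change over four months.

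| Variability known at | Baseline | Follow-up | Contribution to paired comparison |
|---|---|---|---|
| both times | controlled | controlled | no change |
| follow-up only | not controlled | controlled | improvement |
| neither | not controlled | not controlled | no change |

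The second row is the one the protocol makes likely: entry is screened on HbA1c, and sensor wear follows a medication change.

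**5. Size.** Let r be the share of the 20 with a usable recording, p the share meeting a level-based criterion, and g the share meeting variability ≤ 36%, independent of p. The extra patients counted as controlled are 20 × r × (1 − p) × g. The article gives none of these three, so all values are assumptions. With p = 30% (6 patients) and g from 50% to 90%:

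- r = 0: none extra.
- r = 0.5: 20 × 0.5 × 0.7 × 0.5 = 3.5, to 20 × 0.5 × 0.7 × 0.9 = 6.3.
- r = 1: 7.0 to 12.6, so 13.0 to 18.6 counted instead of 6.

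Each patient is 1/20 = 5 percentage points. The last line is a ceiling for these assumed rates.

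**The case against.** The strongest case accepts the logic and disputes its reach.

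- **Recordings are not universal.** A reader might infer that most of the diabetic group would be scored as controlled. The article does not support that: sensor wear depends on a medication change, Visit 4 carries no monitoring mark, and HbA1c or blood glucose is what is scheduled at every visit. This stands, and it limits the four-month proportion more than days to first control.
- **A false improvement does not follow from *or* alone.** If all three criteria were applied at both times, a patient with stable high glucose would be controlled at both and show no change. This also stands. The bias needs variability to be missing at baseline, which the exclusion criterion and monitoring schedule make likely but do not guarantee.
- **Relapse.** A reader might assume that glycaemic relapse inherits the same flaw. Both mentions of relapse gloss it as high blood pressure only, so the article does not show that the glycaemic definition is used there.
- **The term is undefined and its cited source is not at hand.** This matters little: a measure of spread relative to the mean leaves the level free.
- **It is a feasibility study.** The article says it does not aim to establish efficacy, and its only stated success criterion concerns agreement on dosing. This lowers the severity. It does not rescue the definition, because the outcomes are still to be reported as preliminary effects and used for later planning.

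**Conclusion.** The definition is wrong as written. Variability ≤ 36% is sufficient alone and, read as SD/mean, sets no limit on glucose level: traces with means of 12, 14 and 16 mmol/L and 32%, 11% and 1% of time in range all count as controlled. That result needs only the reading of variability and a distribution for the trace; the normal check gives 28%, 12% and 3%.

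Among diabetic patients with a sensor recording, this can inflate the control proportion and shorten days to first control. Where the recording exists only after entry, it also biases the before/after comparison towards improvement. The amount ranges from nothing, if no patient has a usable recording, to a large share of the 20 if all do, and the article does not allow a narrower statement.

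Severity: should-fix. The clinical outcomes are preliminary, one of two disease groups is affected, and no decision rule or sample size rests on glycaemic control.

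**What to change.** In section 2.3.5, remove glycaemic variability as a stand-alone route to control and report it as a separate descriptive outcome. Control then rests on the two level-based criteria, HbA1c or time in range. The clinical limits themselves are for the investigators.

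State that the same level-based criteria apply at baseline and at follow-up, for control at four months and for days to first control. Time in range comes from the same sensor, so where a patient has no baseline recording the paired comparison should use a criterion available at both times. If glycaemic relapse is to be reported, say so and use the same definition.

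A milder alternative is to let variability count only jointly with a level-based criterion.

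Cost: a few lines of text and no new data collection. The reported control proportion will be less favourable, and paired comparisons on time in range will be limited to patients recorded at both times.

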## 3. Discussion

We aim to establish if the CURATE.AI system can practically be used for chronic disease patients and how it can be best operationalised through this feasibility study. We will explore if users find the system acceptable, identify factors that can help or hinder its use, and understand its potential for scaling. In addition, we will investigate ways to improve the algorithm. For example, the inclusion of other variables (i.e., patient characteristics), the simultaneous optimisation of multiple drugs, and the incorporation of other AI algorithms. The data generated from this study will inform the development of the CURATE.AI system and a future efficacy evaluation. Through the development of this application, we hope it may be possible to optimise dosing more rapidly, prevent adverse reactions, and reduce the burden of therapy.

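### Every effect measure for the diabetic group depends on crossing a control threshold; no analysis of HbA1c change is named, although HbA1c change justifies the follow-up length.

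*Protocol article*

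**What the plan says.** The protocol article, section 2.3.1, sets the size: "Forty patients (*n* = 20 hypertensives and *n* = 20 type II diabetics) will be recruited from the outpatient clinic at Alexandra Hospital". Its exclusion criteria remove patients whose HbA1c or blood pressure is already controlled.

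Section 2.3.5 states the main clinical comparison: "The proportion of patients achieving blood pressure control and glycemic control will be calculated by comparing the baseline reading to the four-month follow-up". Control status is then tested within subject by a chi-squared or McNemar test. For diabetes the status has three alternative routes: "Glycaemic control is defined as HbA1c < 7% [40] or glycaemic variability ≤ 36% or time in normal range (4.0 to 10.0 mmol/L) > 70" per cent. Two further measures rest on the same status. One is time to control: "The number of days until blood pressure or glycaemic control is first achieved will be calculated". The other is relapse once control has been reached.

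For blood pressure alone, section 2.3.5 adds: "The proportion achieving clinically relevant reductions in systolic and diastolic blood pressures by the four-month follow-up will be determined". No cut-off is given for a relevant reduction, and there is no HbA1c or glucose counterpart.

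Section 2.3.3 defends the four-month follow-up for diabetes on the ground that, for HbA1c, "emergent evidence suggests clinically relevant changes may occur as early as one month". Table 1 lists HbA1c or blood glucose at Baseline and at Visits 1 to 4. Section 2.3.2 says the clinical outcomes are there to show preliminary effects and that efficacy is not the aim. The Discussion adds: "The data generated from this study will inform the development of the CURATE.AI system and a future efficacy evaluation".

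**The concern.** The follow-up length is argued from how far HbA1c can move, but no named analysis measures how far it moved. A control proportion mixes two things: what happened under the dosing system, and how far from the threshold the patients started. On the HbA1c criterion, a fall from 10.5% to 7.5% is not a success and a fall from 7.1% to 6.9% is.

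The three-way definition can also err in the other direction. Glycaemic variability describes spread, so it can meet its limit while HbA1c is unchanged. Under section 2.3.3 the sensor is worn only after a medication change, starting fifteen days later. No sensor reading is therefore scheduled before the first change, and one near month four depends on a late change.

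At stake is how readable the preliminary effect is in half the study, and whether the report gives an SD of HbA1c change. A later trial with HbA1c change as its outcome would need that SD.

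**Working it through.** **1. Outcomes set side by side (sections 2.3.2 and 2.3.5)**

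| Measure | Diabetes | Hypertension |
|---|---|---|
| Proportion controlled at four months | threshold | threshold |
| Days to first control | same threshold | same threshold |
| Relapse after control | same threshold | same threshold |
| Proportion with a relevant reduction | none | yes, cut-off not stated |
| Mean within-patient change | none named | none named |

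The asymmetry is a missing reduction outcome for diabetes. Neither group has a named continuous change.

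**2. How many falls could go unrecorded on the HbA1c criterion?**

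The article gives no power, effect size or SD, so there is no figure of its own to reproduce.

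- From the document: n = 20; HbA1c criterion < 7%.
- Assumed: the entry exclusion means baseline HbA1c ≥ 7%. Baseline is normal, truncated at 7%, with the means and SDs below. The fall is normal, with mean/SD 0.5/0.8, 0.8/0.8, 1.0/1.0 or 1.5/1.0 points.
- Final HbA1c = baseline − fall. Missed share = P(final ≥ 7% given fall ≥ 0.5 point), by simulation.
- Sensor criteria: missed share × (1 − q), where q is the assumed, independent chance that such a patient meets a sensor criterion.

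| Baseline mean/SD before truncation | Mean after truncation | Missed, HbA1c only | Missed, q = 0.5 |
|---|---|---|---|
| 7.5/0.5 | 7.64 | 9–21% | 4–11% |
| 8.0/1.0 | 8.29 | 33–54% | 16–27% |
| 8.5/1.2 | 8.75 | 48–69% | 24–34% |
| 9.0/1.5 | 9.27 | 61–78% | 30–39% |

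The largest missed share is 0.78 on HbA1c alone, about 0.59 at q = 0.25, 0.39 at q = 0.5 and 0.20 at q = 0.75.

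**3. How much does the starting level drive the result?**

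With 0 of 20 below 7% at entry, the exact two-sided McNemar p-value for r converters is 2 × 0.5^r. Five converters give 0.0625 and six give 0.031, so six are needed. Power = P(Binomial(20, p) ≥ 6), where p is the chance of ending below 7%.

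Take one fixed effect, a mean fall of 0.8 with SD 0.8:

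| Baseline | p | McNemar power |
|---|---|---|
| 7.5/0.5 | 0.57 | 1.00 |
| 8.0/1.0 | 0.35 | 0.74 |
| 8.5/1.2 | 0.24 | 0.35 |
| 9.0/1.5 | 0.17 | 0.11 |

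A paired t-test on the change has noncentrality (0.8/0.8) × √20 = 4.47 and power 0.99 in every row.

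The comparison does not always favour the paired test. For a fall of 0.5 (SD 0.8), noncentrality is (0.5/0.8) × √20 = 2.80 and power is 0.76. McNemar power at baseline 7.5/0.5 is 0.93. That second figure needs care: nobody starts below 7%, so crossings can only be downward, and random variation alone produces some.

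**4. Precision with n = 20**

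- 6/20 controlled: exact 95% CI 11.9 to 54.3%.
- Paired mean change, t(0.975, 19) = 2.093: half-width 2.093 × 1.0/√20 = 0.47 point for an assumed SD of 1.0, or 2.093 × 0.8/√20 = 0.37 for an assumed SD of 0.8.

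**The case against.** The strongest reply has four parts.

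- **The article condenses a fuller plan.** A descriptive change summary is something that plan could supply, and section 2.3.5 promises means with SDs where suitable. This stands in part. But that sentence names no variable and no change score, and the article does list its outcomes, with a reduction measure for one group only.
- **The follow-up rationale is not contradicted.** Reaching control is a clinical improvement, and evidence that HbA1c can move within the period supports the length without committing the study to a change outcome. This stands: there is a mismatch of emphasis, not a contradiction.
- **Nothing is lost for good.** Where HbA1c is measured at both visits, the SD of change can be computed later. This stands with a condition: Table 1 allows glucose instead of HbA1c, so the pair of values is not assured.
- **The study disclaims efficacy.** This stands and keeps the weight modest.

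Two stronger readings are tempting. A reader might infer that most real falls in HbA1c will count as no effect. The documents do not support this: they give no baseline distribution, the missed share spans 9 to 78% on HbA1c alone, and meeting either sensor criterion also counts as control. A reader might also infer that hypertensive patients get a measure of the size of change. They do not; theirs is another proportion, with no cut-off stated.

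**Conclusion.** The point holds in a limited form. As written, the plan describes glycaemic effect only through a three-route control status. The HbA1c route depends on where patients started, and the sensor routes can be met without a fall in HbA1c. Some real falls would not register on the HbA1c criterion, possibly many if baseline is well above 7%.

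How many cannot be determined from the documents. The shares in the working rest on assumed baselines, falls and SDs, and the sensor adjustment rests on an assumed, independent q. The firm part is structural: one fixed effect gives very different control proportions as baseline varies, while the within-patient change is not tied to the threshold.

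This is a worthwhile, low-cost improvement to a feasibility study, not a flaw that undermines it.

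**What to change.** In section 2.3.5, add for the diabetic group the within-patient change in HbA1c from Baseline to Visit 4, as a mean with SD and 95% CI. Label it a descriptive single-arm change and not evidence of efficacy; patients selected for high values can fall without any effect of dosing. Report the change in systolic and diastolic pressure in the same way, so that both groups are treated alike. Keep the control proportions. In Table 1, require HbA1c rather than glucose alone at Baseline and Visit 4.

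The cost is a line or two of analysis text, plus HbA1c becoming compulsory at two visits. Table 1 already schedules renal and liver function at those same visits, so blood is presumably being drawn then. A virtual Visit 4 would still need a sample.

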Compliance with clinic follow-up will be calculated based on the number of scheduled sessions compared to attendance. Compliance with home monitoring will also be determined by remote receipt of data at scheduled time points. The proportion compliant with the home-monitoring schedule and the proportion of patients who drop out from the study will be reported. The number of disagreements between the CURATE.AI dosing recommendations and the physician’s opinion will be quantified. Success of the alignment on dosing decisions is defined as agreement with ≥70% of dosing decisions generated by CURATE.AI. The proportion of participants reaching this criterion will be derived. We will also summarise the reasons for disagreement and the magnitude of differences in dosing decisions, if it occurs. A sub-analysis will be conducted for participants whose dosing decisions were all based on CURATE.AI recommendations versus those who had one or more dosing decisions overridden by the treating physician. The purpose is to explore whether adherence to CURATE.AI confers an advantage in achieving clinical outcomes. Significance will be set at *p* < 0.05.

For interviews, audio recordings of the interview will be transcribed and translated into English (if necessary). A second independent researcher will check the accuracy of the translation. Data will be analysed using a thematic analysis method. Data will be coded according to the meaning of the sentences, followed by developing sub-themes and main themes. Qualitative data will also be organised according to the framework domains (Table 2).

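### The pre-post test of disease control is chosen by the wrong rule, and because controlled patients are excluded at entry its p-value can fall below 0.05 without any treatment effect

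*Protocol article*

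**What the plan says.** Section 2.3.5 (Data Analysis) says that the proportion achieving control "will be calculated by comparing the baseline reading to the four-month follow-up". The test follows: "A within-subject analysis of hypertensive and glycemic control will be conducted using the Chi^2^ or McNemar’s test, if cell counts are small (<5". The same section ends its quantitative part with "Significance will be set at" p < 0.05, and adds: "Clinical outcomes will be analysed separately for the hypertensive and type II diabetic groups".

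Section 2.3.1 gives the size of each group: "Forty patients (*n* = 20 hypertensives and *n* = 20 type II diabetics) will be recruited". Its exclusion criteria include: "Patients with controlled HbA1c or blood pressure at baseline".

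Section 2.3.2 says the main purpose is feasibility and "not to establish efficacy or effectiveness". The limitations section adds that there is no control group. Regression to the mean is not mentioned.

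**The concern.** Two separate things look wrong.

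- **The choice of test.** The comparison is of the same patient at two times. Pearson's Chi-square on the two proportions treats them as separate samples. A small-cell rule properly chooses between an asymptotic and an exact version of one test. It cannot choose between an unpaired and a paired test.
- **The null hypothesis.** McNemar's test asks whether moves into control and out of control are equally likely. If nearly everyone starts uncontrolled, moves out of control are nearly impossible, so the null fails as soon as anyone reads below threshold later. Patients chosen for high readings will tend to read lower next time even if nothing has changed.

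At stake is an efficacy-type p-value, from a study without controls, that a reader could take as evidence that the dosing system works.

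**Working it through.** The protocol gives no power calculation or expected control rate, so there is no figure of its own to reproduce.

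**Inputs from the protocol:** n = 20 per disease group, analysed separately; paired baseline and four-month status; controlled patients excluded; threshold p < 0.05 (two-sided assumed, since sidedness is not stated).

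**Step 1. Which test would the rule select?** A paired 2×2 table has four cells summing to 20. All four reach 5 only if the table is exactly 5/5/5/5. Any other table goes to McNemar. With 0/20 controlled at baseline, one row is empty, so McNemar again applies. If expected counts are meant, in the layout of 0/20 against k/20 the smallest expected count is k/2. Chi-square is then used only when k ≥ 10, where both tests are significant (at k = 10, Chi-square p = 0.0003 and exact McNemar p = 0.002).

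**Step 2. What does McNemar test with 0/20 at baseline?** Let k be the number controlled at four months. Losses of control are 0, so:

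- exact McNemar: p = 2 × 0.5^k
- asymptotic McNemar: statistic = (k − 0)²/(k + 0) = k, on 1 df

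| k of 20 | exact p | asymptotic p |
|---|---|---|
| 4 | 0.125 | 0.046 |
| 5 | 0.0625 | 0.025 |
| 6 | 0.031 | 0.014 |

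The result depends on k alone. It is significant from 6/20 (30%) by the exact version or from 4/20 (20%) by the asymptotic one. The protocol does not say which version is meant.

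**Step 3. Chance of p < 0.05 with no treatment effect, by assumed spontaneous conversion rate.** This is P(K ≥ 6) or P(K ≥ 4) for K ~ Binomial(20, rate):

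| Assumed rate | exact (k ≥ 6) | asymptotic (k ≥ 4) |
|---|---|---|
| 10% | 0.01 | 0.13 |
| 20% | 0.20 | 0.59 |
| 30% | 0.58 | 0.89 |
| 40% | 0.87 | 0.98 |

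**Step 4. What rate could regression to the mean produce?** All inputs here are assumptions: systolic pressure only, between-patient SD 12 mmHg, entry on a reading of at least 140, no true change, and control at month 4 meaning a reading below 140.

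| Assumed true mean; visit-to-visit SD | read <140 at month 4 | P(k ≥ 6) | P(k ≥ 4) |
|---|---|---|---|
| 145; 8 | 19% | 0.16 | 0.54 |
| 145; 10 | 23% | 0.29 | 0.69 |
| 150; 6 (low end) | 10% | 0.01 | 0.13 |
| 140; 10 (high end) | 30% | 0.58 | 0.89 |

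If entry required two readings of at least 140 (a further assumption), the two central rows fall to P(k ≥ 6) of about 0.04 and 0.09.

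**Step 5. Is baseline control really 0/20?** Not necessarily.

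- The exclusion names HbA1c, but the glycaemic outcome is also met through glycaemic variability or time in range.
- Blood pressure control can be met by more than one route: "Blood pressure control is defined as a home or ambulatory blood pressure of less than 135/85 mmHg or office readings below 140/90 mmHg", or a target set by the physician.
- Section 2.3.3 allows calibration visits between recruitment and baseline.

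If some patients are controlled at baseline, the choice of test can alter the p-value. With 7 gains, 1 loss, 5 controlled at both times and 7 at neither, the unpaired Chi-square gives p = 0.057 and exact McNemar 0.070. Under an observed-cell rule this table still goes to McNemar, because one cell is 1. Under an expected-count rule it goes to Chi-square: 6/20 against 12/20 has a smallest expected count of 18/2 = 9.

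**The case against.** **The unpaired test will hardly ever be run.** This largely stands. Step 1 shows that the plan's rule leads to McNemar in nearly every table under observed counts. The sentence is still wrong, but a reader who infers that Chi-square will be the working test, or that it will drive a false positive, goes further than the plan allows.

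**The study disclaims efficacy and admits it has no control group.** This also stands, and it limits the weight of the point. No primary endpoint, sample size or go/no-go rule uses this p-value. The disclaimer does not remove the planned test or the p < 0.05 criterion.

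**The false-positive figures rest on invented inputs.** This is fair. The protocol gives no means or SDs. The model uses systolic pressure alone and selects on one reading, although section 2.3.1 admits patients with established poor control. Nothing comparable has been computed for the diabetic group.

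Three stronger readings are tempting but not supported:

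- That the test *will* give significance without an effect. The range runs from about 1% to 58%, so it *can*.
- That nobody could be controlled at baseline. Step 5 shows routes by which some could be, and the protocol does not settle how many.
- That this is the only clinical inference planned. Section 2.3.5 also compares fully adherent with overridden participants, and the significance level is stated directly after that.

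**Conclusion.** The point holds in limited form. The rule for choosing the test is incorrect as written, with little practical effect at n = 20. The more important defect is that excluding controlled patients makes McNemar's null untenable, so p < 0.05 says nothing reliable about treatment. Moving to a paired test does not cure this.

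The thresholds of 6/20 (exact) and 4/20 (asymptotic) follow from arithmetic, given 0/20 controlled at baseline. The false-positive chance of about 16-29% in the central case and 1-58% over the range (exact test) depends on assumed systolic inputs and single-reading selection. Repeated-reading selection lowers it.

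This should be fixed, but it does not threaten the study's feasibility purpose.

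**What to change.** 1. Delete the Chi-square/McNemar sentence and state that p < 0.05 does not apply to this outcome.
2. Report, for each disease group, the number controlled at Visit 4 over all who entered, with an exact (Clopper-Pearson) 95% CI. For example, 10/20 gives 27-73%. Show beside it how many already met the outcome definition at baseline.
3. Report paired mean changes in systolic pressure, diastolic pressure and HbA1c with 95% CIs. Add a plain statement that selecting uncontrolled patients brings regression to the mean into all of these.
4. If a paired binary test is kept, specify exact McNemar whatever the cell counts, and say that the entry criteria make it uninformative about treatment effect.
5. If the 2018-2020 outpatient extract is set alongside, call it usual-care context. Those patients were under routine care, so their control rate mixes dose changes with regression to the mean and is no clean benchmark for the latter.

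Items 1 to 4 are wording and simple tabulation of data already collected. The cost is that no p-value for control will be available to quote. Item 5 is optional and needs more work, because the protocol describes no fixed four-month visit in that extract.
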